#### Exploratory results

3.2.3

The peripheral blood samples of patients will be collected at baseline and on the 7th and 14th days of treatment, and the differentially expressed genes will be analyzed by full transcriptome sequencing. Simultaneously, the expression of related factors and proteins in peripheral blood will be detected by qRT-PCR and ELISA, to explore the mechanism of the Fusu mixture.

### Safety assessment

3.3

From baseline to the end of the study, physical examinations will be performed daily. Routine blood and urine tests, routine stool tests with occult blood, liver and renal function tests, Coagulation function and electrocardiograms will be examined at baseline and on days 3, 7, and 14, and any adverse events during the study period will be observed and recorded in detail.

### Adverse events (AEs)

3.4

Any adverse medical event occurring in the subjects during the clinical study, regardless of whether it has a causal relationship with the study drug, is considered an AE. The AE report form will be completed during the test. Record the occurrence time, severity, duration, measures taken, and results of adverse events. If a serious adverse event occurs, it should be reported to the adverse drug reaction testing center of the local authority within 24 hours and to the sponsor at the same time.

### Quality control and data management

3.5

Prior to the study, the protocol was reviewed and revised by clinicians, statisticians, and methodologists. All staff of the trial must participate in a series of training sessions to ensure that the involved personnel fully understood the protocol and standard operating procedures to ensure the accuracy and integrity of clinical data. The test supervisor will monitor the process of the test on a regular basis. The evaluator will first record all the data on the paper version of the CRF, and then double input it into the electronic data capture system electronically. Monitoring personnel will regularly check the completion and compliance of CRF. In order to ensure the objectivity of the data, we will ensure that observers and statisticians do not understand the data. An independent quality inspector will monitor the entire process.

### Statistical analysis

3.6

Before analysis, 2 similar participants with complete data will be carefully examined to ensure that the data is correct. All data analyses will then be based on treatment intention.

The data will be analyzed using the statistical software package SPSS 22.0 (Chicago, IL). The analysis method will be selected according to the distribution characteristics of the data. The measured data will be expressed as the mean ± the standard deviation. First, the normal test and the homogeneity test of variance will be performed. In the case of normal distribution and equal variance, a *t*-test will be performed; otherwise, a nonparametric test will be utilized. The difference will be statistically significant when *P* ≤ .05.

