### Sample size

2.4

Calculating the sample size was based on the 28-day mortality. According to the available literature, the 28-day mortality of the western medicine treatment group is about 40%, whereas that of the treatment group with integrated traditional Chinese and Western medicine is about 30%. The software Power Analysis and Sample Size version 11.0 (PASS 11.0) was used to calculate the sample size of the 2 groups, assuming that the test level is *α* = 0.05, the probability of making mistakes *β* = 0.2, considering the 10% loss rate, a total of 620 patients will be enrolled.

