#### Primary outcome

3.2.1

The 28-day mortality will be compared between the 2 groups.

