#### Secondary outcomes

3.2.2

Changes in the following indicators will be detected before and after treatment on days 3, 7, and 14.

(1)Serum levels of inflammatory markers: Validation markers including serum CRP and PCT, IL - 6, TNF-α.(2)Blood gas analysis: Record the arterial blood gas analysis before and after the intervention (Lac, PɑO_2_ / FiO_2_)(3)Assessment of disease severity: The APACHE II and SOFA scoring systems before and after treatment used to compare the scores of the 2 groups. Improvement rate of APACHE II score = (post-treatment score - pre-treatment score) / pre-treatment score. The APACHE II scoring system can be used as an indicator to evaluate the condition and prognosis of ICU patients, which is composed of three parts: Acute Physiology Score (APS), age score and chronic health status score, the final score is the sum of the three parts and the highest score is 71. A higher score indicates worse disease. The SOFA score can be used to assess the occurrence and severity of organ dysfunction in critically ill patients, and the worst value of the day should be adopted for counting. The higher score indicates the worse prognosis.(4)The number of days without ventilator: The number of days without a ventilator will be recorded from the patient's admission to ICU to the completion of 2 courses of treatment.(5)Length of stay: The time from the patient's admission to the ICU to his/her departure from the ICU.(6)ICU mortality: The proportion of deaths in the 2 groups in the total number of participants from the beginning of the trial to 14 days will be recorded.

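### Section 3.6 makes no use of baseline severity: a pre-specified severity-adjusted analysis of 28-day mortality would gain precision from data already collected

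*Protocol article*

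**What the plan says.** The primary outcome in section 3.2.1 is a single sentence: "The 28-day mortality will be compared between the 2 groups". The outcome is binary, and section 2.4 sizes the trial on two proportions, about 40% on Western medicine and about 30% on the integrated treatment, "assuming that the test level is *α* = 0.05, the probability of making mistakes *β* = 0.2", with 10% loss and 620 patients in total.

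Section 3.6 opens its account of methods with "The analysis method will be selected according to the distribution characteristics of the data". The next sentence turns to measured data, summarised as mean and standard deviation. Normality and equal variance are checked. A t-test follows if both hold; "otherwise, a nonparametric test will be utilized". The section adds analysis by intention to treat and a threshold: "The difference will be statistically significant when *P* ≤ .05". It names no covariate and does not say whether the test is one- or two-sided.

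Section 3.2.2 has APACHE II, SOFA and PaO2/FiO2 recorded before treatment as well as after. Of APACHE II it says: "The APACHE II scoring system can be used as an indicator to evaluate the condition and prognosis of ICU patients". It also says that a higher SOFA score means a worse prognosis. It makes no such statement about PaO2/FiO2. All three are used only as secondary outcomes.

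**The concern.** In ventilated patients with sepsis-induced ARDS, the risk of death by day 28 is likely to vary with severity at entry. When a baseline score predicts the outcome, a comparison that ignores it treats explainable variation as noise. The estimate stays unbiased over randomisations, but it is less precise, and a chance difference in severity between the arms is not corrected in the trial at hand.

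This trial already collects two scores that it regards as prognostic, so the precision could be had by changing the analysis wording. A second, smaller matter is that section 3.6 lets the data determine the test and does not exempt the primary outcome. For a mortality endpoint nothing needs to be decided from the distribution, so that freedom serves no purpose there.

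**Working it through.** **Inputs from the documents.** Mortality 40% v 30%, α = 0.05, β = 0.2, 10% loss, N = 620, allocation 1:1 (sections 2.4 and 2.5). This gives 310 per arm, or 279 per arm after 10% loss (0.9 × 310), 558 in all.

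**Inputs not in the documents.** The sidedness of the test, and how well baseline severity predicts 28-day death. Both are treated as assumptions and varied.

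**Step 1: reproduce 620.**

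- One-sided, unpooled variance: n = (1.645 + 0.842)² × (0.4×0.6 + 0.3×0.7) / 0.10² = 278.2, so 279 per arm; 279/0.9 = 310 per arm; total 620. This is exact.
- Two-sided, pooled variance: n = [1.960√(2×0.35×0.65) + 0.842√(0.24 + 0.21)]² / 0.10², giving 356 per arm; 356/0.9 rounds up to 396; total 792. This does not match.

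The stated total therefore fits a one-sided 0.05 calculation, although the protocol does not call it one. The gain from adjustment is accordingly shown for both cases.

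**Step 2: unadjusted power.** Two-sided power = Φ{[0.10 − 1.960√(0.455/n)] / √(0.45/n)}.

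- n = 310: (0.10 − 0.0751)/0.0381 = 0.654, power 74.3%.
- n = 279: (0.10 − 0.0791)/0.0402 = 0.519, power 69.8%.
- One-sided (1.645 in place of 1.960): 83.4% and 79.8%.

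**Step 3: gain from adjustment, by simulation.** There were 6,000 trials per setting, with one standardised normal baseline score and the marginal risks held at 40% and 30%. The unadjusted two-proportion z-test was compared with the Wald test for arm from a logistic model with arm and score. The single score stands for the combined prognostic content of the baseline measures. Gains are in percentage points of power.

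| AUC of score | Variance explained | Two-sided gain, 310/arm | Two-sided gain, 279/arm | One-sided gain, 310/arm | One-sided gain, 279/arm |
|---|---|---|---|---|---|
| 0.50 | 0% | 0.0 | −0.2 | −0.1 | −0.2 |
| 0.61 | 3.6% | 2.2 | 1.4 | 0.8 | 1.3 |
| 0.65 | 6.4% | 2.6 | 2.3 | 1.6 | 2.3 |
| 0.69 | 10.8% | 4.3 | 4.7 | 3.0 | 3.4 |
| 0.74 | 16.9% | 7.1 | 7.4 | 5.5 | 6.3 |
| 0.78 | 23.0% | 9.5 | 11.2 | 7.5 | 8.4 |
| 0.81 | 28.7% | 12.6 | 13.4 | 9.4 | 10.8 |

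The Monte Carlo standard error of each simulated power is about √(0.75×0.25/6000) = 0.6 points. With no true effect and AUC 0.74, the adjusted two-sided test rejected in 4.9% of trials, so the nominal level is kept.

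**Step 4: analytic check on the risk-difference scale.** Adjustment that explains a share R² of the outcome variance acts roughly like n/(1 − R²) patients. With R² = 0.10, 279 per arm behaves like 279/0.90 = 310, and power goes from 69.8% to 74.3%, a gain of 4.5 points. With R² = 0.15 the gain is 6.6 points at 310 per arm and 6.9 at 279. Both agree with the simulation.

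**Reading the table.** Interpolating, a two-sided gain of 3 to 8 points corresponds to an AUC of about 0.66 to 0.76.

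**The case against.** Several points on the other side are sound.

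- A reader might infer that section 3.6 assigns a t-test or a rank test to mortality. The text does not support this. The rule follows a sentence about measured data, and section 3.2.2 lists many continuous outcomes to which it naturally applies. Even if it were applied to 0/1 data, a tie-corrected rank test equals the Pearson chi-square times (N − 1)/N, here 619/620, so the P value would hardly change.
- A reader might count the missing mortality test, effect measure and interval as defects. A journal article commonly leaves these to the full protocol or analysis plan, neither of which is shown. The two-proportion sizing already implies a comparison of proportions. The silence alone is not the point here.
- An unadjusted analysis is valid in a randomised trial and matches the way the trial was sized. Its type I error already allows for chance imbalance. Adjustment is an improvement, not the correction of an error.
- The size of the gain cannot be derived from the documents. Eligibility (ventilated, PaO2/FiO2 no higher than 200, with expected early death and end-stage multi-organ failure excluded) narrows the severity range and could lower the AUC. The simulation also used one generic score, not the exact model proposed.

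What remains is that the only tests named are unadjusted, that test selection from the data is not ruled out for the primary outcome, and that scores the protocol regards as prognostic are at hand and unused.

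**Conclusion.** The point stands as a worthwhile improvement at almost no cost. Confidence is high that section 3.6 makes no use of baseline severity, and moderate about how much adjustment would gain.

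Under 40% v 30% and a two-sided 0.05 test, the gain is about 3 to 8 points of power if the AUC is about 0.66 to 0.76, and about 1 to 13 points over 0.61 to 0.81. If the test is one-sided, it is about 2 to 6 points over 0.65 to 0.74. If severity carries no prognostic information, nothing is gained and essentially nothing is lost.

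Two stronger conclusions should be resisted. A reader might infer that the trial falls short of its 80% power and that adjustment is needed to rescue it. That holds only for a two-sided test, and the protocol does not state the sidedness; one-sided, 620 is what its own inputs give. A reader might also take all three baseline measures as declared prognostic, but the protocol says so only of APACHE II and SOFA.

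**What to change.** Pre-specify the primary analysis as logistic regression of death by day 28 on treatment arm, baseline APACHE II and baseline SOFA, in all randomised patients. Baseline PaO2/FiO2 and ICU (general or respiratory) may be added if named in advance. From this model:

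- report the standardised (marginal) risk difference with its 95% confidence interval. This is the scale on which the trial was sized, whereas the model's conditional odds ratio is a different quantity;
- state whether the test is one- or two-sided;
- give the unadjusted chi-square test and risk difference as support;
- say that the method for this outcome is fixed and not chosen from the data, and confine the normality and variance rule to the measured outcomes.

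The cost is analysis wording plus a pre-stated rule for missing baseline scores. No further patients or measurements are needed.

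### Mean ± SD is fixed as the summary for all measured data, including variables the plan sends to a nonparametric test, so their printed summary would not describe what was tested

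*Protocol article*

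**What the plan says.** Section 3.6 (Statistical analysis) first says what the distribution decides: "The analysis method will be selected according to the distribution characteristics of the data". The next sentence sets the summary and attaches no condition: "The measured data will be expressed as the mean ± the standard deviation". After the checks of normality and variance, the test is chosen in two branches: "In the case of normal distribution and equal variance, a *t*-test will be performed"; "otherwise, a nonparametric test will be utilized". The nonparametric test is not named. The article mentions no median, interquartile range, transformation or rank-based estimate.

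The continuous secondary outcomes under this rule are in section 3.2.2. They include inflammatory markers ("Validation markers including serum CRP and PCT, IL - 6, TNF-α"), lactate within the blood gas item ("Record the arterial blood gas analysis before and after the intervention") and ICU length of stay ("The time from the patient's admission to the ICU to his/her departure from the ICU"). The primary outcome in section 3.2.1, 28-day mortality, is binary and does not fall under the rule.

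**The concern.** A rank test asks whether values in one arm tend to exceed those in the other. A mean and SD answer a different question, and with a long right tail a few patients largely set them. If a marker is non-normal enough to leave the *t*-test branch, the plan prints a summary on one scale and a P value from another. It names no estimate that belongs to the test.

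At stake is how the secondary results can be read. A reader could see that a marker differed between arms but not by how much. The SD could exceed the mean for a quantity that cannot be negative. In some circumstances the printed means could lean the opposite way from the test.

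**Working it through.** **Text.** The mismatch follows from section 3.6 alone: one fixed summary and two possible tests. It needs only that the nonparametric branch is used, which the plan itself foresees. The plan derives no figure on this point, so there is none to reproduce. The rest gauges size.

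**Inputs.** From sections 2.4 and 2.5: 620 patients, 1:1, 10% loss, so 620/2 = 310 per arm and 310 × 0.9 = 279 analysed per arm. Assumed, because the article gives no spread: log-normal values at one visit, medians 100 (control) and 75 (Fusu mixture), log-scale SD *s* of 0.5, 1.0 or 1.5. Each scenario was simulated 4,000 times.

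**Is the branch used?** The article does not name its normality test. With Shapiro-Wilk (an assumption), normality was rejected in at least one arm in all 200 runs checked per scenario.

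**How far does mean ± SD stray?** For log-normal data, mean = median × exp(*s*²/2) and SD/mean = √(exp(*s*²) − 1).

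- *s* = 1.0: SD/mean = √(2.718 − 1) = 1.31. Control 165 ± 216, treatment 124 ± 162. One SD below the control mean is 165 − 216 = −51.
- *s* = 1.5: SD/mean = √(9.488 − 1) = 2.91. Control 308 ± 897, treatment 231 ± 673, against medians of 100 and 75.

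**Do means and ranks disagree in direction?**

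| Log-SD, control v treatment | Opposite direction, all trials | Opposite direction, significant Mann-Whitney only |
|---|---|---|
| 0.5 v 0.5 | 0% | 0% |
| 1.0 v 1.0 | 0.4% | 0.1% |
| 1.5 v 1.5 | 10% | 5.6% |
| 0.5 v 0.6 | 0% | 0% |
| 1.0 v 1.2 | 29% | 22% |
| 1.0 v 1.3 | 64% | 57% |
| 1.0 v 1.5 | 97% | 96% |

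With equal spread, disagreement is sampling noise. With unequal spread it can be systematic. The expected means cross when the treatment log-SD reaches √(*s*₀² + 2 ln(100/75)), which at *s*₀ = 1.0 is √(1 + 0.575) = 1.26. At 1.0 v 1.3 the means are 165 and 175, favouring control. The ranks favour treatment: the probability that a treated value exceeds a control value is 0.43.

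**Does the test lose power?** With equal spread, Mann-Whitney was significant in 92% of trials at *s* = 1.0 and 59% at 1.5. For a log-scale *t*-test the approximate power is Φ(0.288/(*s*√(2/279)) − 1.96). That is Φ(3.40 − 1.96) = 92% at *s* = 1.0 and Φ(2.27 − 1.96) = 62% at 1.5. The rank test gives up little.

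**The case against.** The best defence is that this is a descriptive convention in a condensed article. Mean ± SD is how data are to be displayed; the plan never calls it the effect estimate. The sentence before it ties the method to the distribution and might be read as covering the display too. Medians and rank-based intervals are often left to a statistical analysis plan, so their absence is no fault. The nonparametric branch also catches normal data with unequal variances, where mean ± SD is a fair summary.

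Part of this stands. The plan does not declare the mean to be the estimand, and the mismatch does not affect every variable in that branch. But the fault is a stated rule, not a missing detail. As worded, the distribution governs the method of analysis, and the summary is then fixed for all measured data. An analysis plan that followed the sentence would carry the mismatch forward.

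A reader might infer three stronger things, none of which the documents support:

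- **The printed means will often contradict the test.** With equal spread they rarely do. The high rates need spread to differ between arms, about which the article says nothing.
- **The plan wastes patients or power.** A comparison of raw log-normal means would need (exp(*s*²) − 1)/*s*² times as many patients as a log-scale analysis, or 1.7 at *s* = 1.0 and 3.8 at 1.5. The plan does not make that comparison for non-normal data; it uses a nonparametric test.
- **The trial's main conclusion is at risk.** The primary outcome is binary, and neither the sample size nor alpha depends on this sentence.

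**Conclusion.** The point holds as a reporting defect of minor to moderate weight, confined to continuous secondary outcomes. Where non-normal data trigger the nonparametric test, the prescribed summary does not describe what was tested and can be dominated by a few extreme values. This follows from the text without any simulation.

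The size rests on assumptions: that CRP, PCT, IL-6, TNF-α, lactate and ICU stay are right-skewed, roughly log-normal, with log-SDs of about 1.0 to 1.5. On that footing the SD is 1.3 to 2.9 times the mean. With equal spread, at most about 5% of significant rank tests sit beside means of opposite direction. The illustration uses values at a single visit. Section 3.2.2 speaks of changes over days 3, 7 and 14, and change scores could be more or less skewed.

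**What to change.** Replace the summary sentence in section 3.6 with a rule that follows the test, for example: approximately normal variables are reported as mean ± SD with the mean difference and 95% CI; where data are non-normal and the nonparametric test is used, they are reported as median (IQR) with the Hodges-Lehmann difference and 95% CI.

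The Hodges-Lehmann difference is the median of all between-arm pairwise differences, so its sign agrees with the direction of the Mann-Whitney statistic. It is not, in general, the difference between the two medians, and the report should say so.

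For the strictly positive markers, an acceptable alternative is to prespecify a log-scale analysis with the geometric mean ratio and 95% CI. Either choice would do, but it should be made before unblinding.

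The cost is one or two sentences and slightly more output. No new data are needed, and sample size and alpha do not change. The only downside is that results for skewed variables would read as median shifts or ratios instead of differences in means.

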### Informed consent

3.7

Consent will be provided to patients who meet the study requirements, including the study name, research background, research method, what participants should do in the study, inclusion/exclusion criteria, treatment plan, and obligations, possible side effects of the trial drug, costs in the participation process, and so on. We will make every effort to protect the privacy of the patient's personal medical data to the extent permitted by law. Participation in this study is voluntary, and the basic Western medicine treatment program will continue for patients who do not participate or withdraw. When patients sign informed consent, their personal and medical information will be used in this study.

### Secrecy

3.8

Participants’ medical records will be kept in hospitals and will be accessible to researchers, research institutions, and ethics committees. No public report on the results of this study will reveal the personal identity of the participants. We will make every effort to protect the privacy of the participant's personal medical data to the extent permitted by law. Personal and medical information will be kept confidential in a safe and reliable place. Participants can request access to their personal information (such as an address, contact information, etc) at any time, and can modify this information if necessary.

## Discussion

4

Population-based data suggest that the incidence rate of ARDS is 1.5–8.3 per 100 thousand person-years, and it is likely to double in the next ten years.^[24,25]^ Currently, there is no specific drug for the treatment of ARDS. Our previous clinical observation and basic research showed that the Fusu mixture has auxiliary therapeutic effect on ARDS patients. However, so far, there is no large sample study on the efficacy and safety of Fusu mixture in the treatment of sepsis-induced ARDS.

Simultaneously, the existing literature shows that there is no report on the mechanism of Chinese medicine treating ARDS caused by sepsis based on the whole transcriptome. Therefore, it is necessary to carry out prospective tests to determine the clinical efficacy and safety of Fusu mixture and explore its mechanism.

There are limitations in this study. First, since the study was conducted in Chengdu, Sichuan Province, it is not clear whether the clinical effects of the investigational drug differ in other regions and races. Secondly, due to the limited funds and conditions, the follow-up time is short and the follow-up indicators are limited. If the trial is successful, it will provide patients and doctors with new options to treat ARDS, so as to achieve effective treatment of the disease and reduce the disease and economic burden of sepsis-induced ARDS patients and their families. In the future, multicenter randomized controlled trials should be carried out to carry out clinical research on patients with ARDS in a wide range and in multiple regions, and relevant verification should be carried out in combination with the mechanism of action.
